### Sample size calculation

Based on previous research data, the incidence of PHN in patients over 50 years old who receive standard antiviral treatment for HZ is 34.8%, while the incidence of PHN after repeated TPVB injections with lidocaine and triamcinolone is 16.3% (Ma et al., 2022). We predict a similar incidence rate in this study, based on the comparable treatment regimen and patient population. Sample size calculation is performed using PASS V.15 software (NCSS, Kaysville, UT, United States) with α = 0.05, β = 0.1, and power = 90%. Considering a dropout rate of 10%, we plan to recruit 127 patients per group, totaling 254 patients, with a 1:1 randomization ratio.

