### Handling bias and missing data

Multiple imputation will be used to address missing data. For outliers, the decision to correct, remove, or apply data transformation methods will be based on the source and nature of the outliers to mitigate their impact. We will conduct sensitivity analyses to assess the impact of missing data. Potential sources of bias will be addressed through thorough data monitoring and regular audits by the DMC.

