### Primary outcome

The incidence rate of PHN between the two groups will be compared using the chi-square test. Relative risk (RR) and its 95% confidence interval will be calculated to evaluate the relative risk and effect of DXP with ropivacaine compared to antiviral treatment alone. Although randomization should control for most confounding factors, potential confounding factors such as sex age, baseline pain intensity, and comorbidities will be considered and controlled using multivariate logistic regression analysis.We will assess multicollinearity and select the most relevant predictors using methods like stepwise regression.

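### The supporting adjusted PHN model should use covariates fixed in advance, not covariates picked by stepwise regression on the trial outcome

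*Protocol article*

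**What the plan says.** In the protocol article, the Primary outcome paragraph of the statistical analysis section sets out the analysis in this order:

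- The test: "The incidence rate of PHN between the two groups will be compared using the chi-square test".
- The effect measure: "Relative risk (RR) and its 95% confidence interval will be calculated".
- The adjustment, introduced by a remark that randomization should take care of most confounding: "potential confounding factors such as sex age, baseline pain intensity, and comorbidities will be considered and controlled using multivariate logistic regression analysis".
- The choice of model: "We will assess multicollinearity and select the most relevant predictors using methods like stepwise regression".

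The paragraph gives no entry or removal criterion, no closed list of covariates and no statement that the treatment term is retained. No other section supplies these.

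Three other parts of the article bear on how often the model would be fitted. The section on bias and missing data says "Multiple imputation will be used to address missing data". The Statistical analysis section plans both intention-to-treat and per-protocol analyses. The primary outcome definition assesses PHN at 3, 6 and 12 months.

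**The concern.** The last two sentences of that paragraph do not fit together. One says that four named factors will be controlled. The next allows any of them to be removed according to how they relate to PHN in this trial's own data. Because the list is introduced by examples and the method is only illustrated, two competent analysts could follow the text and report different adjusted effects.

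Blinding of the analysts is promised only until database lock, so nothing in the article prevents the model from being settled with outcome and allocation both known. Selection can also give different covariate sets in the two analysis sets, at the three visits and in each imputed dataset. If the adjusted model is fitted at each visit in each set, that is 2 × 3 = 6 separate selections before imputation multiplies them. Agreement between the intention-to-treat and per-protocol results, which the article offers as evidence of robustness, is harder to interpret if the two models adjust for different things.

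The text selects predictors without exempting treatment. If treatment were included in the selection, the adjusted analysis could report no treatment effect at all, or only an effect large enough to have survived.

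**Working it through.** **1. What the trial is sized on.** Inputs from the Sample size calculation section: PHN 34.8% (control) and 16.3% (intervention), α = 0.05 (taken as two-sided), power 90%, dropout 10%.

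n per arm = [z₀.₉₇₅√(2p̄q̄) + z₀.₉₀√(p₁q₁ + p₂q₂)]² / (p₁ − p₂)², with p̄ = 0.2555

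= [1.960 × 0.6168 + 1.2816 × 0.6028]² / 0.185² = 3.926 / 0.034225 = 114.7, so 115.

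Allowing for dropout: 115 × 1.1 = 126.5, so 127; or 115 / 0.9 = 127.8, so 128. The plan's 127 is reproduced to within one patient. The calculation is for two unadjusted proportions, which matches the chi-square test and owes nothing to the logistic model.

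**2. Is selection needed to keep the model small?** Expected PHN cases at the planned rates: 127 × (0.348 + 0.163) = 65 with everyone followed, or 114 × 0.511 = 58 after 10% dropout. Treatment plus four covariates is five terms: 65 / 5 = 13 and 58 / 5 = 11.6 cases per term. A fixed model of that size is affordable. The Introduction already names higher initial pain, older age and comorbid conditions as raising PHN risk, so the data are not needed to find the covariates.

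**3. What selection does to the treatment estimate.** The article gives no covariate effects, so these are assumptions. The simulation had 127 per arm, 1,000 trials per row and six candidates, with log odds ratios of 0.2 for sex, 0.4 per SD for age, 0.5 per SD for baseline pain, 0.3 for one comorbidity and 0 for two others. The intercept and treatment effect were set to give 34.8% and 16.3%, which implies a conditional log odds ratio of −1.09. Backward elimination used either AIC or a likelihood-ratio p < 0.05 rule.

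Treatment always kept in:

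| True log-OR | Model | Mean estimate | Rejects | 95% CI coverage |
|---|---|---|---|---|
| 0 | fixed | −0.01 | 4.9% | 95.1% |
| 0 | AIC / p < 0.05 | 0.00 / 0.00 | 4.6% / 4.5% | 95.4% / 95.5% |
| −0.54 | fixed | −0.56 | 47.8% | 94.0% |
| −0.54 | AIC / p < 0.05 | −0.56 / −0.55 | 46.7% / 46.6% | 94.0% / 93.9% |
| −1.09 | fixed | −1.14 | 94.1% | 94.3% |
| −1.09 | AIC / p < 0.05 | −1.13 / −1.12 | 93.7% / 94.0% | 93.7% / 94.2% |

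Treatment itself open to selection:

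| True log-OR | Dropped (AIC / p < 0.05) | Mean estimate when kept |
|---|---|---|
| 0 | 84% / 95% | about 0 |
| −0.54 | 32% / 53% | −0.72 / −0.82 |
| −1.09 | 1.7% / 5.5% | −1.14 / −1.16 |

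Overstatement at half the planned effect: 0.722 / 0.543 = 1.33 and 0.816 / 0.543 = 1.50, that is 33% and 50%.

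A separate simulation with four assumed covariates agreed. With treatment kept in, stepwise against fixed gave size 5.1% against 4.8%, and at a log odds ratio of −1.0 both had 90% power; coverage was 95% for both. With treatment open to selection, it was dropped in 36% of trials at −0.5.

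**The case against.** The strongest reply is that this touches only a secondary layer of the analysis and does little harm there. Most of that stands.

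- **Role.** A reader might infer that stepwise selection decides the primary result, or that the plan has two rival primary effect measures. The article does not support that. The chi-square test and relative risk come first, the sample size is built on two proportions, and the logistic model enters as an addition to randomization.
- **Treatment term.** A reader might infer that the plan lets treatment be dropped. That rests on silence. The sentence before speaks of confounding factors, so the predictors to be selected are most naturally those factors, and a model built to control confounding of a treatment effect would contain treatment.
- **The high null drop rates.** Losing treatment in 84% of null trials is simply how AIC works: a one-parameter term stays only if its likelihood-ratio statistic exceeds 2 (p < 0.157). It is not evidence about this trial.
- **Imputation.** A reader might conclude that stepwise models cannot be combined across imputed datasets. They can, for example by selecting on pooled tests or stacked data and then fitting one common model. The article excludes neither.
- **Odds ratio beside relative risk.** This is common in a supporting analysis and is not an error.

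The reply does not remove the stated method. This is not a detail left to an analysis plan: the article positively names outcome-driven selection from an open list, and contradicts its own sentence about controlling the four factors.

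**Conclusion.** The point holds as a defect of the supporting adjusted analysis only. As written, that analysis is not reproducible from the text, and its covariates are chosen on the outcome it is meant to estimate. The unadjusted test, the relative risk and the 254-patient sample size are unaffected. On the natural reading, with treatment kept in, type I error, coverage and power barely differ from a fixed model, so the gain is an adjusted estimate fixed before the data are seen, not better error control. On the less natural reading, with treatment open to selection, the estimate would often be missing at modest effects and overstated by about a third to a half when present. The simulated sizes rest on assumed covariate effects and selection rules; the contradiction and the open-ended wording do not. This is a free improvement, not a threat to the primary result.

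**What to change.** Delete the sentence on stepwise selection. Pre-specify one logistic model with treatment always included, plus age, sex, baseline NRS-11 and one defined comorbidity indicator, all retained whatever their significance. Use that same model in every imputed dataset, in both analysis sets and at each visit where it is fitted. State that the chi-square test with the relative risk is the primary analysis and that the adjusted model is supporting. A standardised relative risk from the model is optional, so that the adjusted result is on the planned scale.

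The cost is wording, settled before database lock, with no change to sample size or patient care. The baseline items listed under Study outcomes do not name comorbidities, so confirm that the chosen indicator is on the case report form.

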### Secondary outcomes

For quantitative data (e.g., NRS-11, SF-12, PSQI, and inflammatory markers), t-tests or Mann-Whitney U tests will be used depending on the data distribution characteristics to compare differences between the two groups. For categorical outcomes (e.g., complication rates), chi-square tests or Fisher’s exact tests will be used. Repeated measures ANOVA or mixed models will be employed to analyze time effects and group effects for continuous repeated measures data (e.g., quality of life scores at different time points post-treatment).

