#### Study outcomes

The baseline demographics characteristics of the patients will be collected through searches of the institution’s electronic medical records or direct questioning of the participants. Data collected from the electronic medical records will include gender, age, BMI affected nerves, average weekly consumption of analgesics and levels of inflammatory markers. Data obtained directly from the patients will include pain scores (NRS-11 scores), the Pittsburgh Sleep Quality Index (PSQI), quality of life score, and pain characteristics for comparison with post-intervention outcomes. All patients will undergo systematic follow-up after receiving treatment. The follow-up schedule, outlined in Table 1, is designed to comprehensively assess the long-term outcomes of the treatment. Patients will be followed up at 1, 3, 6, and 12 months post-treatment. These time points were selected based on the natural course of herpes zoster-associated pain and the development of PHN. PHN is typically defined as pain persisting beyond 3 months after the onset of the rash, hence the inclusion of the 3-month mark as a primary time point for assessing PHN incidence (Ahronowitz and Fox, 2018; Ma et al., 2022; Rowbotham and Petersen, 2001). The 1-month and 6-month follow-ups allow for the assessment of intermediate outcomes, such as pain intensity, sleep quality, and inflammatory markers, while the 12-month follow-up provides data on the long-term efficacy and safety of the intervention. The follow-up assessments include the following.

**TABLE 1 T1:** Time schedule of participant enrolment, allocation and assessment.

	Enrolment	Allocation	Post-allocation											Close out
Time point	D0	D0	D1	D2	D3	D4	D5	D6	D7	D14	M1	M3	M6	M12
Enrolment														
Eligibility screening	√													
Informed consent	√													
Allocation		√												
Intervention														
Antiviral therapy			√	√	√	√	√	√	√					
Thoracic Paravertebral Nerve Block Treatment			√							*				
Assessment														
Demographics	√													
Incidence rate of PHN												√	√	√
NRS-11	√	√	√	√	√	√	√	√	√	√	√	√	√	√
Skin lesions	√	√	√	√	√	√	√	√	√	√	√	√	√	√
Pain characteristics and	√	√	√	√	√	√	√	√	√	√	√	√	√	√
SF-12		√							√			√	√	√
PSQI		√							√			√	√	√
Levels of inflammatory markers		√							√			√	√	√
Consumption of analgesics			√	√	√	√	√	√	√	√	√	√	√	√
Adverse events			√	√	√	√	√	√	√	√	√	√	√	√

*If NRS-11 ≥ 4 at D14, a second TPVB, injection may be performed.

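### Continuous secondary outcomes are tested by t-test or Mann-Whitney U, chosen from the data and with no baseline covariate, although each measure is taken at D0

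*Protocol article*

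**What the plan says.** The Statistical analysis part of the Protocol article, under Secondary outcomes, gives two rules for continuous data.

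- For quantitative outcomes, with NRS-11, SF-12, PSQI and inflammatory markers as the examples: "t-tests or Mann-Whitney U tests will be used depending on the data distribution characteristics to compare differences between the two groups".
- For longitudinal data: "Repeated measures ANOVA or mixed models will be employed to analyze time effects and group effects for continuous repeated measures data". The example in that sentence is quality-of-life scores measured after treatment.

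Neither rule names a baseline covariate, a group-by-time term or a visit at which the groups are to be compared.

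Baseline values are collected. Under Study outcomes: "Data obtained directly from the patients will include pain scores (NRS-11 scores), the Pittsburgh Sleep Quality Index (PSQI), quality of life score", together with "pain characteristics for comparison with post-intervention outcomes". The records also supply "average weekly consumption of analgesics and levels of inflammatory markers". Table 1 schedules NRS-11, SF-12, PSQI and the markers at D0.

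The primary analysis does use baseline: "potential confounding factors such as sex age, baseline pain intensity, and comorbidities will be considered and controlled using multivariate logistic regression analysis". That model is for PHN only.

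**The concern.** When the same quantity is measured before and after treatment, its baseline value is often the best single predictor of the follow-up value. A two-sample test leaves that information unused. The protocol accepts covariate adjustment for the binary primary outcome but commits the continuous outcomes, where baseline and outcome are the same measure, to tests that cannot adjust.

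Three things are at stake.

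- **Precision.** Intervals are wider than the data require.
- **Chance imbalance.** A baseline difference between arms carries through to the follow-up comparison.
- **Effect measure.** A t-test addresses a difference in means. Mann-Whitney addresses the probability that a patient in one arm scores higher than a patient in the other. If the distribution decides which is used, the quantity to be reported is not known in advance and may differ between outcomes, or between visits for one outcome.

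**Working it through.** **The plan's own figure.** The only sample size stated is for PHN. The inputs are the rate for those "who receive standard antiviral treatment for HZ is 34.8" per cent, and "the incidence of PHN after repeated TPVB injections with lidocaine and triamcinolone is 16.3" per cent, with α = 0.05 (taken as two-sided), power 90% and 10% dropout. With pooled variance and mean rate 0.2555:

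n = [1.960·√(2·0.2555·0.7445) + 1.2816·√(0.348·0.652 + 0.163·0.837)]² / 0.185² = (1.2089 + 0.7725)² / 0.034225 = 114.7, so 115 per arm.

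Then 115 × 1.1 = 126.5, so 127 (or 115/0.9 = 127.8, so 128). The stated 127 reproduces. The point below does not touch it.

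**Inputs for the secondary outcomes.** The protocol gives no SD, correlation or target difference for any continuous outcome. The values of r (0.3 to 0.7) and the standardised difference of 0.35 are therefore assumptions. Patients analysed: 127 × 0.9 = 114 per arm.

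**Variance of the group difference, relative to a t-test on follow-up values.**

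- Baseline-adjusted (ANCOVA): 1 − r².
- Change score, equal SDs at baseline and follow-up: 2(1 − r).
- Change score, baseline SD equal to k times the follow-up SD: 1 + k² − 2rk = (1 − r²) + (k − r)². This is never below 1 − r², so adjustment is at least as precise whatever k is.

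**Power** = Φ(0.35·√(114/2)/√factor − 1.960) = Φ(2.642/√factor − 1.960). With factor 1 (t-test on follow-up values) this is Φ(0.682) = 75.3%.

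| assumed r | factor, adjusted | factor, change | power, adjusted | power, change |
|---|---|---|---|---|
| 0.3 | 0.91 | 1.40 | 79.1% | 60.8% |
| 0.5 | 0.75 | 1.00 | 86.2% | 75.3% |
| 0.6 | 0.64 | 0.80 | 91.0% | 84.0% |
| 0.7 | 0.51 | 0.60 | 95.9% | 92.7% |

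The same precision without adjustment would need 1/0.91 = 1.10, 1/0.75 = 1.33 or 1/0.64 = 1.56 times as many patients at r = 0.3, 0.5 or 0.6. These factors concern comparisons of means. Mann-Whitney estimates something else and has no factor on this scale.

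**Validity (simulation, 114 per arm, no treatment effect).**

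- The unadjusted t-test rejects in 5.3%, 4.9% and 4.9% of trials at r = 0.3, 0.5 and 0.7.
- Among trials with a baseline imbalance of |z| > 1.5, which has probability 2(1 − Φ(1.5)) = 0.13, it rejects in about 8%, 14% and 21%.
- Choosing the test by a Shapiro-Wilk check in each arm (an assumed form of the protocol's rule) rejects in 5.0% of trials with normal data and 4.6% with lognormal data. With truly normal data the check still switched to Mann-Whitney in 9.7% of trials.

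**The case against.** The best defence has four parts.

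1. **Mixed models are already listed, and a condensed article may leave covariates to the SAP.** This stands for the mixed model's detail. It does not answer the first rule, which states a method. Adopting a baseline-adjusted model would replace the t-test or Mann-Whitney comparison, not elaborate it.

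2. **Baseline may enter through change scores.** The Objectives speak of reduction and improvement, and the outcome list defines the marker outcome as a change. So it cannot be said that the plan ignores baseline. But the text does not say whether follow-up values or changes are tested, and change scores are never more precise than adjustment. With equal SDs they do worse than follow-up values when r is below 0.5.

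3. **The correlations are assumed.** This stands. Entry requires NRS-11 of at least 4, which narrows the baseline range and may lower r for pain, so the upper rows of the table may be optimistic for that outcome.

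4. **Statisticians are blinded until database lock.** This limits steering if the test is chosen before lock. The effect measure is still left unfixed.

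A reader might infer more than the text supports:

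- *The group effect is a main effect diluted by D0 values.* The only repeated-measures example is post-treatment scores, nothing says D0 is kept as a response, and a group-by-time term is not excluded.
- *Repeated-measures ANOVA would lose every patient with a missed visit.* The protocol plans multiple imputation, an ITT analysis of all randomised patients, and mixed models as the alternative.
- *Four methods compete for each outcome.* The protocol names two pairs, one for group comparisons and one for longitudinal data.

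**Conclusion.** The point holds as a minor to moderate one, confined to the continuous secondary outcomes. The stated tests are valid, and overall type I error stays near 5%, also when the test is chosen by a normality check. A claim of inflated error would therefore be wrong; the higher rates apply only to trials with a marked chance imbalance at baseline. The primary outcome and the sample size of 254 are unaffected.

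The cost is avoidable loss of precision and an effect measure that is not fixed in advance. The variance removed by adjustment is 9%, 25% or 36% at r = 0.3, 0.5 or 0.6. With 114 analysed per arm and a standardised difference of 0.35, power would rise from 75.3% to 79.1%, 86.2% or 91.0%. These figures rest on assumed correlations and an assumed difference, and the gain for NRS-11 may lie at the low end. That adjustment is at least as precise as a t-test on follow-up values or on change does not depend on the value of r, apart from a negligible cost in degrees of freedom.

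**What to change.** For each continuous secondary outcome, make the main analysis one baseline-adjusted model:

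- either the mixed model already listed, with post-baseline values as response and baseline value, treatment, visit and treatment-by-visit as fixed effects;
- or ANCOVA at a named visit.

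Report the adjusted mean difference with 95% CI at a visit named in advance, such as M3. Decide beforehand whether CRP, TNF-α and IL-6 are log-transformed. Keep Mann-Whitney as a sensitivity analysis only, and remove the rule that selects the test from the distribution. If analgesic consumption is modelled in the same way, state which value is its baseline: Study outcomes lists one from the records, but Table 1 starts that row at D1.

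The cost is a change of analysis wording, made before database lock. It needs no extra patients, visits or measurements for the four measures named.

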### Ethics and dissemination

This study adheres to the 2013 SPIRIT Statement and the Declaration of Helsinki and has been approved by the Ethics Committee of the Second Affiliated Hospital of Guangxi Medical University (Approval Number: 2024-KY(0505)). All participants must sign an informed consent form before enrollment, detailing the study’s purpose, procedures, potential risks and benefits, and privacy protection measures. This clinical trial is registered on the International Clinical Trials Registry Platform at https://www.chictr.org.cn/index.html (Registration Number: ChiCTR2400087273, Registration Date: 2024-07–24). The results will be disseminated through scientific journals and conferences.

## Discussion

The proposed study aims to investigate the efficacy and safety of ultrasound-guided thoracic paravertebral injection of DXP combined with ropivacaine in treating thoracic ZAP. Given the significant burden of ZAP and PHN on patients' quality of life, this study is of critical importance.

### Strengths and innovations

The innovative aspect of this study lies in its use of DXP, a liposomal formulation of dexamethasone, known for its high lipophilicity and prolonged duration of action. DXP’s pharmacokinetics allow it to be primarily distributed at sites of inflammation, gradually releasing the active compound, which enhances its anti-inflammatory efficacy and minimizes side effects compared to free dexamethasone (Lorscheider et al., 2019). This formulation, combined with ropivacaine, a sodium channel blocker with a long duration of action and small impact on motor function, offers a promising therapeutic approach for managing ZAP (Kaufman et al., 2005; Dresner et al., 2000; Hauritz et al., 2018).

TPVB has shown efficacy in alleviating ZAP and reducing the incidence of PHN. However, single injections are less effective, often requiring multiple injections for optimal effect (Ma et al., 2022; Abdelwahab et al., 2022; Deng et al., 2023; Kim et al., 2017) The proposed study hypothesizes that a single injection of DXP combined with ropivacaine can reduce the incidence of PHN and effectively alleviate ZAP, minimizing the need for repeated injections and thereby reducing the treatment burden on patients and healthcare systems.

